#### Screening and randomisation

Patients will be screened against inclusion and exclusion criteria at the time of diagnosis of ACLF or hepatic decompensation. Those who meet the criteria will be enrolled into the study and provided informed consent. These recruited patients will be randomised in a 1:1 ratio to either the LivR Well programme or to complex care liver clinic in the control arm. Participants will be computer randomised and informed of their allocation by the CLD nurse specialist prior to discharge or within 24 hours of obtaining informed consent. Patients from both study arms will be registered on the Virtual Hospital masterlog through the Microsoft Power Apps program. Due to the nature of the intervention, blinding of study participants or clinical staff administering the LivR Well programme will not be possible. However, outcome ascertainment for the primary outcome, as well as the health services utilisation secondary outcomes will be blinded. Furthermore, all data analyses will be undertaken in a blinded manner. The statistician will be blinded to the feasibility study data results and the treatment allocation of the RCT.

#### Trial status

We anticipate recruitment at a rate of 1-2 participants per week based on the progress of the feasibility study conducted at the same health service. A participant flow chart describing patients from screening, to enrolment, to randomisation, and allocation will be provided and will demonstrate how many patients are eligible for the intervention out of the entire study population.

#### Data collection

All data will be de-identified at the collection and stored securely on a Power BI database. Recruitment, retention and questionnaire completion numbers will be recorded throughout the trial. Biological specimens will be collected for the study and for patient care and analysed and stored through standard hospital processes. Consent will not be obtained for specimens to be used for genetic, molecular analysis, or in future/ancillary studies.

Data collected will includeDemographic information including age, sex, primary languageClinical data at baseline, 28 days and 6-week follow-upPatient-reported outcome measures using EQ-5D and CLDQ quality of life instrumentsHospital admissions, referral for liver transplantation and death

#### Adverse events

Adverse events are defined as “any untoward medical occurrence in a patient or clinical trial participant”. Serious adverse events (SAEs) will be defined as …” an untoward occurrence that results in death; is life-threatening; requires hospitalisation or prolongation of existing hospitalisation; results in persistent or significant disability or incapacity; consists of a congenital anomaly or birth defect” [28]; and will be reported to the PI and local ethics committee immediately. Any patients suffering harm from the trial will receive post-trial care in the liver clinic. Adverse event and SAS data will be collected in the same Power BI database at the time of occurrence by the hepatology nurse consultant.

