#### Design

The RCT will be a multi-site, non-blinded, parallel-group study with two independent population arms to determine the efficacy and safety of the new model of care (LivR Well) compared to standard care and to inform a cost-effectiveness analysis.

This study protocol was developed in line with Recommendations for Interventional Trials (SPIRIT) guidelines including the SPIRIT checklist [17], which has been adapted in accordance with World Health Organisation registration (Appendix 1) and the CONSORT extension to pilot and feasibility trials [18] (Table 3, Appendix 2).

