#### Participants and setting

The study context is a multicentre tertiary health service in Melbourne, Australia with recruitment from three tertiary hospital campuses. Monash Health is the second largest healthcare service in Australia managing a catchment population greater than 1.2 million people [19], which includes the largest Culturally and Linguistically Diverse (CALD) community, the significant burden of socioeconomic disadvantage and the highest unemployment rates in the state of Victoria [20]. The 28-day intervention will be delivered through ‘Hospital in the Home’ (HITH), a medically-led ambulatory care programme supported by physical clinics and home visits by the nursing team. HITH is able to deliver many aspects of acute hospital care in the community to otherwise stable patients including diagnosis and management of acute conditions that would typically require bed-based care

Patients will have access to up to three home visits per week by nursing staff and physiotherapists. The patients will attend a hospital-based ambulatory care liver clinic weekly for a medical and nursing review with a dietitian, social work, addiction medicine, and pharmacist consultations as required. Patients will be referred to LivR Well from an outpatient context, the emergency department or the inpatient ward. Patients with any severity of liver disease are eligible unless receiving end-of-life care. There are no cut-offs for the MELD score or Child Turcotte Pugh score.

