#### Processes, interventions and comparisons

LivR Well is a 28-day intensive liver optimisation programme delivered at home and through the outpatient clinic. It is an innovative multidisciplinary model of care co-developed with patients and carers including delivery system re-design (home-based nursing, weekly medical reviews, regular dietitian and pharmacy consults) and adjunct interventions including enteral nutrition for sarcopenia, physiotherapy, large volume paracentesis, addiction medicine consultation and neuropsychiatric assessment for cognitive impairment/hepatic encephalopathy. Referrals to allied health clinicians will be made based on indications outlined in Table 4.

Patients will be enrolled on discharge from the acute admission, directly from the emergency department or the outpatient clinic as demonstrated in the Patient Journey Map (Fig. 1). A standardised checklist template (Appendix 3) will be completed on admission. Patients will have an in-home clinical review by a nurse up to three times per week with observations and blood tests taken weekly, or as requested by the clinic gastroenterologist. A face-to-face appointment at the ambulatory complex care liver clinic will occur weekly and will provide medical and nursing reviews with the opportunity for a dietitian, pharmacist and social worker consultations as required. Key time points and tasks for completion are outlined in Table 5.

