**Fig. 1 Fig1:**
[figure not shown]
Patient journey map

**Table 5 Tab5:** Key time points and tasks for completion

	Day 1	28-day programme	Week 6	Week 12
Timeframe for completion	Within 3 days	Weekly	Within 7 days	Within 2 weeks
Tasks	Blood tests EQ-5D CLDQ	Blood tests Complex Care Liver Clinic	Blood tests DQ-5D CLDQ	Blood tests Complex Care Liver Clinic

Patients on the LivR Well programme will be remotely monitored in between clinic appointments through a custom-built app paired to a Bluetooth scale. Patient-reported outcome measures (PROMS) including quality of life, will be collected through a mobile phone text message link to the online surveys. Patients will also be able to access Lucy LiverBot, a custom-built artificial intelligence ChatBot for all disease-related questions. Quality of life assessments will be performed at day 1 and longitudinally at 6 weeks and 12 weeks from admission in both arms of the RCT. Two validated instruments will be used [EuroQol 5 Dimensions (EQ-5D) [25] and Chronic Liver Disease Questionnaire (CLDQ)] [26]. Outcomes from these assessments will guide the economic evaluation for a cost-effectiveness analysis. Adherence will be monitored through recording attendance at appointments, home visits and regular urinary ethyl glucuronide tests, a biomarker of alcohol consumption [27].

The comparator will be outpatient management in a ‘complex care liver clinic’, an ambulatory care clinic for patients with decompensated cirrhosis, promoting continuity of care by a gastroenterologist, hepatology nurse and pharmacist through regular face-to-face appointments. The control cohort will have no access to the additional allied health clinicians, technology aids or home visits through the LivR Well programme.

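### Adverse events are logged as they occur while LivR Well patients are seen far more often in days 1-28, so non-serious events are likely to be recorded unequally between arms

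*Protocol article*

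**What the plan says.** The Design section gives the purpose of the trial as "to determine the efficacy and safety of the new model of care (LivR Well) compared to standard care", so a between-arm reading of safety is intended.

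The Adverse events section defines an adverse event as "any untoward medical occurrence in a patient or clinical trial participant", which takes in non-serious events. A serious event includes one that "requires hospitalisation or prolongation of existing hospitalisation". On collection it says: "Adverse event and SAS data will be collected in the same Power BI database at the time of occurrence by the hepatology nurse consultant" (SAS is read here as a slip for SAE). It names no assessment times common to both arms.

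Contact differs by design. Under Processes, interventions and comparisons, "LivR Well is a 28-day intensive liver optimisation programme delivered at home and through the outpatient clinic", and "Patients will have an in-home clinical review by a nurse up to three times per week with observations and blood tests taken weekly". The same section adds a weekly face-to-face clinic for the LivR Well arm, and app and Bluetooth-scale monitoring between clinics. Participants and setting has "Patients will have access to up to three home visits per week by nursing staff and physiotherapists". The comparator is a clinic with regular appointments, at no stated interval, and "The control cohort will have no access to the additional allied health clinicians, technology aids or home visits through the LivR Well programme".

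Screening and randomisation limits blinded ascertainment to the primary outcome and the health-service utilisation outcomes. The Discussion concedes that close follow-up may change how soon patients are readmitted. It does not mention adverse-event detection.

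**The concern.** An outpatient event that does not lead to hospital can be logged only if somebody sees it or is told of it. When one arm is observed several times a week and the other at clinic visits only, the count of such events measures surveillance as well as harm. After day 28 the extra surveillance of the LivR Well arm normally stops, so the recording conditions also change within that arm.

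What is at stake is how the non-serious events are read. An excess under LivR Well could be closer watching or real harm, and data collected this way would not tell the two apart. The trial might then report a false signal against the programme, or explain away a true one.

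**Working it through.** The plan gives no figure on this point to reproduce. The check counts the contacts and then asks how far unequal contact could move the recorded rates.

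**Contacts in days 1-28, LivR Well**
- Home visits: up to 3 a week × 4 weeks = 12 (Participants and setting; Processes, interventions and comparisons), taking nurse and physiotherapist visits to share the cap of three.
- Clinic: 1 a week × 4 weeks = 4.
- Total: 12 + 4 = 16 at most, or one every 28/16 = 1.75 days.

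**Contacts in days 1-28, control**
- The frequency is not stated. Assumed range: 4, 2 or 1 visits, that is, every 7, 14 or 28 days. The contact ratio is then 4:1, 8:1 or 16:1.

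**Model A: an event is recorded only if a contact falls while it is present.** Equal true rates are assumed. For event duration d and contact interval g, P(recorded) = min(1, d/g). With g = 1.75 the LivR Well value is 1 for both durations below, so the ratio is 1 divided by the control value.

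| Event duration | Control every 7 days | Every 14 days | Every 28 days |
|---|---|---|---|
| 7 days | 1/(7/7) = 1.0 | 1/(7/14) = 2.0 | 1/(7/28) = 4.0 |
| 3 days | 1/(3/7) = 2.3 | 1/(3/14) = 4.7 | 1/(3/28) = 9.3 |

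If patients instead recall every event at their next contact, P(recorded) is 1 in both arms and the ratio is 1.0 throughout.

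**Model B: each contact picks up an event with probability q.** P(recorded) = 1 − (1 − q)^k for k contacts. The range q = 0.1 to 0.3 is an assumption.

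| q | LivR Well, k = 16 | Control, k = 4 | Ratio | Control, k = 2 | Ratio | Control, k = 1 | Ratio |
|---|---|---|---|---|---|---|---|
| 0.1 | 0.815 | 0.344 | 2.4 | 0.190 | 4.3 | 0.100 | 8.2 |
| 0.3 | 0.997 | 0.760 | 1.3 | 0.510 | 2.0 | 0.300 | 3.3 |

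**What this could do to a comparison.** Suppose 40% in each arm truly have a non-serious event (assumption) and controls are seen weekly. Under Model B the recorded proportions are:
- q = 0.1: 0.4 × 0.815 = 0.326 against 0.4 × 0.344 = 0.138
- q = 0.3: 0.4 × 0.997 = 0.399 against 0.4 × 0.760 = 0.304

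The chance that a two-sided 5% test of two proportions shows an excess is Φ[(difference − 1.96·SE₀)/SE₁], with SE₀ pooled and SE₁ unpooled:

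| Per arm | q = 0.1 | q = 0.3 |
|---|---|---|
| 160 (hepatic decompensation) | 98% | 43% |
| 60 (ACLF) | 69% | 19% |

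These are illustrations only: the plan states no such test, and the models use the ceiling of 16 as if every contact took place. Neither model gives a ratio below 1.0.

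**The case against.** The strongest reply is that the collection sentence describes data entry: who enters events, where and when. It does not say how events are sought, and it does not say that they are found only at contacts. A journal article commonly leaves elicitation to the full protocol, which may hold a common schedule. The control clinic also has a hepatology nurse. More contact is the intervention itself, so some unequal detection is unavoidable in an unblinded trial of a care model.

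Much of this stands as a limit on size. Sixteen contacts is a ceiling, the control interval is unknown, and recall at the next visit would remove most of the gap. It does not remove the point. The article states an occurrence-based method beside surveillance that differs by arm, and the blinded ascertainment it describes does not extend to adverse events.

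A reader might go further and infer that the safety comparison as a whole is biased, that LivR Well is bound to show more adverse events, or that a several-fold excess is to be expected. The documents do not support this:
- Weekly control visits with 7-day events give a ratio of 1.0 under Model A.
- The large ratios need sparse control visits, short events and no recall, none of which is stated.
- Data collection includes hospital admissions and deaths, so the most serious events can be compared on a common basis.
- Safety is not among the primary or secondary outcomes under Outcomes, and Statistical analyses plans no adverse-event test.

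**Conclusion.** The point holds for non-serious adverse events. At equal true rates they are likely to be recorded more often under LivR Well in days 1-28. The direction follows from the stated contact patterns. The size cannot be fixed from the documents: it rests on the control visit interval, event duration, recall and the chance of detection per contact, all of which are assumed above, and it could be nil.

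Deaths and hospitalisations are less exposed. They are not wholly immune, since the Discussion accepts that readmission may itself depend on the intensity of follow-up. No primary or secondary outcome is affected. This is a cheap improvement worth making, and it does not put the trial's main conclusions at risk.

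**What to change.** In the Adverse events section, base the between-arm safety comparison on two sources:

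1. Deaths and hospitalisations taken from hospital records in the same way for both arms.
2. Other adverse events elicited with one short checklist, asking about events since the last shared assessment, at day 28, week 6 and week 12 in both arms.

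The trial already uses these time points: disease severity is assessed at day 28 and week 12 (Outcomes), and clinical data are collected at 28 days and week 6 (Data collection). List events found only at home visits, by remote monitoring or on programme blood tests descriptively for the LivR Well arm, without comparing them with control. Add unequal detection of non-serious events to the limitations in the Discussion, next to the existing remark on readmission.

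The cost is a wording change and slight extra work at existing contacts. The downside is that fewer non-serious events enter the comparison, though the descriptive listing keeps the rest visible.

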#### Interim analysis

A data monitoring committee will consist of 3 senior independent clinician researchers without competing interests. An interim analysis will be conducted and we will adopt a Bayesian approach for an adaptive trial design where efficacy and futility criteria will be based on the probability of treatment effects, given the observed data in our feasibility study. One interim analysis will be performed in the ACLF and decompensated cohort when 50% of patients have been randomised and have completed 12 weeks of follow-up. We will stop the RCT for efficacy if the posterior probability (Pr) that the hazard ratio (HR) is < 1 is > 90% (Pr (HR <1|data) > 0.9. Similarly, we would stop for futility if Pr (HR <1|data) < 0.1. The results are reviewed by the independent data monitoring committee who will ultimately guide the decision to continue or cease the study.

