**Methods:**

We will recruit adult patients with chronic liver disease from the emergency departments, in-patient admissions, and an ambulatory liver clinic of a multi-site quaternary health service in Melbourne, Australia. A total of 120 patients meeting EF-Clif criteria will be recruited to the ACLF arm, and 320 patients to the hepatic decompensation arm. Participants in each cohort will be randomised to the intervention arm, a 28-day multidisciplinary programme or to standard ambulatory care in a 1:1 ratio. The intervention arm includes access to nursing, pharmacy, physiotherapy, dietetics, social work, and neuropsychiatry clinicians. For the ACLF cohort, the primary outcome is 28-day mortality. For the hepatic decompensation cohort, the primary outcome is 30-day re-admission. Secondary outcomes assess changes in liver disease severity and quality of life. An interim analysis will be performed at 50% recruitment to consider early cessation of the trial if the intervention is superior to the control, as suggested in our feasibility study. A cost-effectiveness analysis will be performed. Patients will be followed up for 12 weeks from randomisation. Three exploratory subgroup analyses will be conducted by (a) source of referral, (b) unplanned hospitalisation, and (c) concurrent COVID-19. The trial has been registered with the Australian New Zealand Clinical Trials Registry.

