#### Sample size

Sample size calculations were performed for each of the ACLF and hepatic decompensation arms using a 2-sided alpha of 5%, a power of 80%, and an anticipated 20% dropout.

For the ACLF cohort, we used the primary endpoint 28-day mortality, based on published rates of 22–74%, with a rate of 33.9% demonstrated in a study of 1343 hospitalised patients at 29 liver units in 8 European countries [2]. A 75% reduction in mortality in the intervention group generates a mortality rate of 8.5%, a conservative estimate considering our feasibility study of 59 participants resulted in a 3% 28-day mortality rate. We calculate a total sample size of 120 participants or 60 in each arm for the ACLF cohort. For the hepatic decompensation cohort, the sample size calculation is based on the primary endpoint of 30-day re-admission, which is estimated 17–38% [3, 29, 30]. Re-admission rates in our feasibility were 50% lower than anticipated at 18% by 30-days therefore we used an anticipated 17% 30-day re-admission rate in the intervention arm. We calculate a total sample size of 320 or 160 in each arm for the hepatic decompensation cohort. . Sample size calculation was performed using Stata statistical software, version 16.1 for Mac (StataCorp, College Station, TX, USA).

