#### Statistical analyses

The data analysis for the primary composite endpoint of death, referral for liver transplantation or 30-day readmission from the date of hospital discharge will be undertaken on an intention-to-treat basis. A 28-day mortality rate will be calculated from the date of randomisation. For the primary and other binary outcomes, chi-squared tests will be used to compare the intervention and control groups. Survival analyses will also be undertaken, with the generation of Kaplan-Meier curves and Cox regression analyses to derive (adjusted) hazard ratios. For continuous outcomes, t-tests or non-parametric equivalents (e.g., Mann-Whitney tests) will be applied to compare the intervention and comparator groups. A *p* value of 0.05 is considered significant and 95% confidence intervals will be reported for all effect estimates Three exploratory subgroup analyses are planned: (a) comparing groups by the source of referral—conducted to address bias created following randomisation whereby in-patients in the intervention arm may be discharged home earlier due to perceived safety with regular home visits compared to those in the control arm. This subgroup analysis will account for differences between those admitted from in-patient admission compared to the emergency department or the ambulatory liver clinic; (b) comparing groups by re-enrolment to LivR Well after drop out due to unplanned re-admission to hospital. Data from the first enrolment to LivR Well will be included in the primary outcomes on an intention-to-treat basis and (c) patients with COVID-19 at the time of referral. Analyses will be performed using Stata statistical software, version 16.1 for Mac (StataCorp, College Station, TX, USA).

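### The decompensation cohort's primary is re-admission alone in three places and a composite including death in a fourth, and the stopping hazard ratio names no event, so the handling of death without re-admission is unsettled

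*Protocol article*

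**What the plan says.** Three sections of the Protocol article define this cohort's primary without death. The Abstract (Methods) states "For the hepatic decompensation cohort, the primary outcome is 30-day re-admission". Outcomes (Primary outcomes) lists the same endpoint. Sample size says "the sample size calculation is based on the primary endpoint of 30-day re-admission, which is estimated 17–38" per cent, and derives 320 patients from it.

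Statistical analyses departs from this. It refers to a "primary composite endpoint of death, referral for liver transplantation or 30-day readmission from the date of hospital discharge" and does not limit it to either cohort. The same section plans chi-squared tests for the primary and other binary outcomes, and Cox regression for hazard ratios. It does not say how death enters an analysis of re-admission.

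Interim analysis sets one look per cohort, "when 50% of patients have been randomised and have completed 12 weeks of follow-up". The efficacy rule is "We will stop the RCT for efficacy if the posterior probability (Pr) that the hazard ratio (HR) is < 1 is > 90" per cent, and the futility rule is "we would stop for futility if Pr (HR <1|data) < 0.1". Neither rule names an event or a time window. The results go to an "independent data monitoring committee who will ultimately guide the decision to continue or cease the study".

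Death is collected (Data collection) and is a serious adverse event (Adverse events). Mortality is the primary only in the ACLF cohort. In the Outcomes section it is neither primary nor secondary for the decompensation cohort.

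**The concern.** The two definitions treat the same patient in opposite ways. Take someone who dies at home on day 20 without having been re-admitted. Under the composite, this is an unfavourable event. Under re-admission alone, the chi-squared table counts the patient as not re-admitted, which is the favourable cell. In a Cox model the patient is either censored or kept at risk without an event.

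This matters for a home-based programme because the arms may differ in where and when deterioration is met. Statistical analyses accepts that intervention inpatients may go home sooner, and the Discussion accepts that knowledge of allocation may shift re-admission thresholds. If some deaths at home occur in patients who would otherwise have been re-admitted, fewer re-admissions may reflect more deaths. A stopping hazard ratio built on re-admission alone could then move towards efficacy for the wrong reason. Because the event is unnamed, the plan does not settle whether its rule has this property.

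**Working it through.** **1. The plan's own figure.** Sample size gives 17% in the intervention arm, two-sided alpha 5%, power 80% and 20% dropout. It gives no single control rate, so 320 can only be back-solved:

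n per arm = [1.96·√(2p̄(1−p̄)) + 0.8416·√(p₁(1−p₁) + p₂(1−p₂))]² / (p₁−p₂)²

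With p₁ = 0.32, p₂ = 0.17 and p̄ = 0.245: [1.192 + 0.504]² / 0.0225 = 127.9, so 128 per arm. Then 128/0.8 = 160 per arm, or 320 in total. A re-admission contrast of 32% vs 17% therefore reproduces 320 exactly. No rate for a composite is given, which is consistent with the size resting on re-admission alone.

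**2. Interim size.** 50% of 320 is 160, about 80 per arm.

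**3. Assumptions for the illustration.**
- No true benefit: 34.4% are heading for re-admission within 30 days in both arms. This rate is from Background and concerns ACLF admissions, so it is only a stand-in here.
- Flat prior. The plan refers to the feasibility data but specifies no prior.
- 30-day home deaths without re-admission: 2–5% control and 5–15% LivR Well. The documents give no death rate for this cohort, so this is an assumed range.

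**4. A single table.** Take 28/80 control re-admissions, the same underlying need in both arms, and k LivR Well patients who die at home instead of being re-admitted. With Beta(1,1) posteriors, Pr(LivR Well rate < control rate) is:

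| k | Re-admitted | Pr |
|---|---|---|
| 0 | 28 vs 28 | 0.50 |
| 4 | 24 vs 28 | 0.75 |
| 7 | 21 vs 28 | 0.88 |
| 8 | 20 vs 28 | 0.91 |
| 10 | 18 vs 28 | 0.96 |

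On proportions the 0.90 threshold is crossed at 8 such deaths. A crude log rate ratio is closer to a hazard ratio. For 20 vs 28, ln(20/28) = −0.336 with SE √(1/20 + 1/28) = 0.293, so Pr = Φ(1.15) = 0.87. For 19 vs 28, −0.388/0.297 gives Φ(1.30) = 0.90, just over the threshold, so that scale needs 9. Counting the deaths as events returns Pr to 0.50 in every row.

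**5. Simulated chance of an efficacy stop.** Cox model, 80 per arm, 30-day horizon, stop if Pr(HR<1) > 0.90, 2,500 runs per scenario (Monte Carlo error about 1 percentage point or less). Columns show how the dead are handled.

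| Home deaths, control vs LivR Well | Censored at death | Kept at risk as non-events | Death counted as event |
|---|---|---|---|
| *Deaths replace re-admissions* | | | |
| 5% vs 5% | 10% | 10% | 9% |
| 2% vs 5% | 18% | 20% | 11% |
| 5% vs 10% | 25% | 27% | 10% |
| 2% vs 10% | 36% | 42% | 10% |
| 5% vs 15% | 50% | 58% | 10% |
| *Deaths independent of re-admission* | | | |
| 5% vs 10% | 10% | 12% | 5% |
| 5% vs 15% | 11% | 16% | 1% |

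**6. Hand check of the replacement rows.** At 5% vs 10%, observed re-admission is 0.344−0.05 = 0.294 vs 0.344−0.10 = 0.244. For a one-sided 10% test with 80 per arm:

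Φ{[0.05 − 1.2816·√(2·0.269·0.731/80)] / √((0.294·0.706 + 0.244·0.756)/80)} = Φ{(0.05 − 0.0899)/0.0700} = Φ(−0.57) = 0.28

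At 5% vs 15% (0.294 vs 0.194): Φ{(0.10 − 0.0870)/0.0674} = Φ(0.19) = 0.58. Both agree with the simulated 27% and 58%.

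**The case against.** The strongest reply is that the analysis section already counts death. Under that composite, excess home deaths do not raise the stop chance. This stands, and it means the fault is a conflict between sections, not a settled choice of re-admission alone. It does not remove the fault, because the outcome definition and the sample size both say otherwise.

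A second reply is that the hazard ratio's event is unnamed and the look follows 12 weeks of follow-up, so calling it a re-admission hazard ratio is inference. This also stands: the stopping consequence is conditional.

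Third, a Cox model that censors at death does not by itself credit a home death to LivR Well. This is correct when deaths are independent of re-admission (10–11%). The bias needs displacement, or the dead kept as non-events.

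Fourth, the illustration is adverse by construction. Feasibility 28-day mortality was 3%, and seven or fewer displaced deaths do not meet the rule in the single-table example. The figures show direction and possible size, and are not a forecast.

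A reader might go further and infer that the programme keeps unstable patients at home, that excess deaths would trigger a stop, and that the monitoring committee would not see them. The documents do not support this. Participants and setting describes home care for people who are otherwise stable. The committee reviews the results and guides the decision, so no stop is automatic. Serious adverse events "will be reported to the PI and local ethics committee immediately", but the text does not say that only they are told, and Data Availability makes the team accountable to an independent safety board throughout. What that board receives by arm is detail an article may leave to other documents.

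**Conclusion.** The point holds as an unreconciled primary endpoint together with an unnamed stopping event. If re-admission alone is followed, the chi-squared comparison counts death at home without re-admission as a favourable result. A re-admission hazard ratio is then biased towards LivR Well where deaths displace re-admissions or the dead are kept as non-events.

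In the displacement case with no true benefit, the chance of an efficacy stop goes from about 10% to 25–27% (home deaths 5% vs 10%) or 50–58% (5% vs 15%). It stays at about 10–11% when death is an event. These sizes rest on assumed death rates, a flat prior, 80 per arm and a re-admission rate borrowed from ACLF admissions. The baseline of about 10% comes from the 0.90 threshold itself and is not part of this point.

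The documents do not establish that the trial will stop for efficacy because of deaths. They leave open a definition under which deaths could push it that way.

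**What to change.** Bring the Abstract, Outcomes, Sample size and Statistical analyses sections to one primary for the decompensation cohort, in which death without re-admission within 30 days is an unfavourable outcome. State whether transplant referral belongs in it and from which date the 30 days run. In Interim analysis, name that same endpoint and its 30-day window as the event behind the hazard ratio in both stopping rules, and show all-cause mortality by arm beside it. Make the change before anyone has seen interim results by arm.

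The cost is a few sentences and no new data, since deaths are already collected. The event rate rises slightly, so the rates behind the 320 must be restated for the chosen endpoint, including the control rate that the section now leaves out. An early efficacy stop becomes somewhat harder to reach.
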